## Abstract

**Background:**

Improving retention in prevention of mother to child transmission (PMTCT) of HIV programs is critical to optimize maternal and infant health outcomes, especially now that lifelong treatment is immediate regardless of CD4 cell count). The WelTel strategy of using weekly short message service (SMS) to engage patients in care in Kenya, where mobile coverage even in poor areas is widespread has been shown to improve adherence to antiretroviral therapy (ART) and viral load suppression among those on ART. The aim of this study is to determine the effect of the WelTel SMS intervention compared to standard care on retention in PMTCT program in Kenya.

**Methods:**

WelTel PMTCT is a four to seven-centers, two-arm open randomized controlled trial (RCT) that will be conducted in urban and rural Kenya. Over 36 months, we plan to recruit 600 pregnant women at their first antenatal care visit and follow the mother-infant pair until they are discharged from the PMTCT program (when infant is aged 24 months). Participants will be randomly allocated to the intervention or control arm (standard care) at a 1:1 ratio. Intervention arm participants will receive an interactive weekly SMS ‘How are you?’ to which they are supposed to respond within 24 h. Depending on the response (ok, problem or no answer), a PMTCT nurse will follow-up and triage any problems that are identified.

The primary outcome will be retention in care defined as the proportion of mother-infant pairs coming for infant HIV testing at 24 months from delivery. Secondary outcomes include a) adherence to WelTel; (b) adherence to antiretroviral medicine; (c) acceptance of WelTel and (d) cost-effectiveness of the WelTel intervention.

**Discussion:**

This trial will provide evidence on the effectiveness of mHealth for PMTCT retention. Trial results and the cost-effectiveness evaluation will be used to inform policy and potential scale-up of mHealth among mothers living with HIV.

**Trial registration:**

ISRCTN98818734; registered on 9th December 2014

## Background

### HIV and maternal and newborn health in Kenya

Identification and rollout of the most cost-effective interventions to eliminate HIV infections and AIDS death among women and children is a key priority for Kenya. According to the AIDS Response Progress Report 2014, the number of people living with HIV (PLHIV) in Kenya has increased by 15 % over the last 4 years, reaching 1.6 million cases in 2013, with an estimated incidence of100 000 new HIV infections in 2014 [1]. Women represent about 57 % of all PLHIV in Kenya and close to 1 % (101,000) of all Kenyan children are living with HIV, corresponding to 10 % of all PLHIV [1]. As many as 11 000 Kenyan children were estimated to be newly infected in 2013, mainly through mother to child transmission (MTCT). Thus, Kenya’s commitment to eliminate MTCT of HIV by 2015 will not be achieved, but improvements have been made. Over the last decade, the number of HIV-infected pregnant women in need for PMTCT in Kenya has also declined, albeit too slowly, from 98,000 in 2004 to 79,000 in 2013 [1]. Since 2013, Kenya has adopted PMTCT Option B+, the World Health Organization guideline recommending all pregnant women living with HIV receive immediate HIV treatment *for life* regardless of immune defense (CD4 count), a strategy called PMTCT Option B+ [2].

Antiretrovirals (ARVs) during pregnancy, delivery and breastfeeding, and for the infant 6 weeks post-delivery can reduce the risk of transmission from 35 % to <2 % in low-income countries [3]. Key strategies to finally eliminate MTCT include increased knowledge of PMTCT, increased involvement from the male partner, universal attendance of antenatal care (ANC) by pregnant women, universal testing of pregnant women for HIV and provision of ARVs from early pregnancy throughout the breastfeeding period, and facility delivery [4]. Kenya’s progress on these goals is uneven. While the proportion of pregnant women tested for HIV has increased from 68 to 92 % in the last 5 years [1], only 5 % of male partners accompanied their pregnant partner to ANC [1]. PMTCT coverage (the number of pregnant women living with HIV started on ARVs before delivery) declined in Kenya from 86 % in 2010 to 73 % in 2013, i.e. 58,000 out of 79,000 pregnant women living with HIV were offered PMTCT services [1]. This was partly due to the multiple challenges of implementing Option B+, which is much more resource demanding.

Only 50 % in need of PMTCT were given ARVs within 6 weeks of their HIV diagnosis [1], a service delay that may cause avoidable MTCT. Only 45 % of all HIV-exposed infants were tested for HIV, i.e. the majority of children were lost to follow up leading to preventable child deaths [1]. Because of these shortcomings, the proportion of HIV-exposed children who became HIV-infected has halted at 14 % in the last 3 years. If Kenya is to achieve the global target of eliminating MTCT of HIV, initially aimed for 2015, this trend needs to be reversed through new and more effective interventions.

### Mobile phone use for information and health service strengthening in Kenya

The rapid expansion in mobile phone technology in Africa has created new opportunities for information sharing and service delivery where other infrastructure, such as cable connectivity and constant electricity supply is inadequate. In 2013, 82 % of Kenyan households owned a mobile phone [5], reaching 100 % of 20–29 year-olds i.e. the age-period when most women give birth [6]. In fact, Kenya has the world’s highest proportion of cell phone owners (80 %) who use mobile banking, and 60 % of Kenyans living on less than $2,50 i.e. under the poverty line, have mobile phones [6].

Mobile technology for health (mHealth) is increasingly being used to overcome shortcomings in information systems, laboratory equipment and human resource capacity in low-income countries. Within maternal and child health care (MCH), mobile technology has been used to link ANC with pregnant women and new mothers [7], to remind community health workers in rural areas [8] and to submit surveillance reports on disease outbreaks and delivery of services [9]. Other uses of mHealth include registration of records [10] and monitoring of drug procurements [11, 12].

Several trials have highlighted the potential of mHealth to improve HIV services e.g. in adherence to ART, retention in ART care, and even for receipt of laboratory HIV test results [13–15]. A recent Cochrane review, which included the WelTel RCT in Kenya found compelling evidence that weekly text messages to non-pregnant HIV infected patients are effective [16] in improving ART adherence.

Whether a weekly interactive SMS intervention (the WelTel model) improves adherence and retention in PMTCT care and encourages life-long ARVs is unknown. The situation for pregnant women living with HIV in a country like Kenya is often highly complicated. Many women do not feel comfortable disclosing their HIV status to a partner or family members in fear of being stigmatized and socially isolated [17], which greatly influences adherence to ART and PMTCT. Furthermore, most women are newly diagnosed with HIV during pregnancy, often asymptomatic and have little time to adjust to the idea of living with HIV before they must start on ARVs. Our previous research shows that competing burdens, including breadwinning responsibilities, stigma, feelings of guilt and fear of transmitting HIV to the baby, fear of abandonment and violence from the male partner also affects women’s capacity to adhere to PMTCT [18].

The WelTel trial remains the only SMS adherence intervention study with the lowest risk of bias ranking. The WelTel service has other advantages in that it is low cost since it uses SMS to check-in on patients, can work with minimal literacy since problems can be followed up with voice calls and extends into the population that do not own their own phones since shared access is sufficient, and by being open-ended check-ins allows almost any problem to be triaged. We will assess the effectiveness, including evaluation of costs of weekly interactive SMS reminders to improve the retention of pregnant women and mother-infant pairs in PMTCT care in Kenya. Ultimately this will result in better PMTCT coverage and reduced infant HIV infections.

### Research hypothesis

The weekly interactive mobile phone SMS (WelTel) is an effective as well as cost-effective method to improve the retention of women living with HIV and their newborns’ in PMTCT care (women living with HIV and their HIV exposed infants who successfully complete the program when infant is aged 24 months).

### Study objectives

#### Primary objective

To determine effectiveness of the WelTel SMS intervention on retention of women living with HIV and their newborns’ in PMTCT care in urban and rural Kenya.

#### Secondary objectives

To assess adherence to the WelTel SMS intervention among pregnant women and newly delivered mothers living with HIV.To determine adherence to single components of PMTCT among pregnant women and newly delivered mothers living with HIV (ARVs, facility-based delivery, early infant HIV testing and exclusive breastfeeding).To explore facilitators for and barriers to using WelTel SMS in order to inform any improvements on the model for PMTCT among pregnant women and newly delivered mothers living with HIV as well as PMTCT staff.To evaluate costs from a payer’s perspective, of the WelTel SMS for retaining women living with HIV and HIV-exposed infants in clinical follow-up until 24 months post-delivery (discharge from PMTCT).

## Methods/design

### Trial design

The WelTel PMCT study is a 4–7 center two-arm open randomized controlled trial in which the intervention is allocated in a 1:1 ratio (Fig. 1 trial design).

**Fig. 1 Fig1:**
[figure not shown]
WelTel PMTCT trial design

### Study setting

The study is in western Kenya and involves 4–7 facilities that are among over 192 facilities providing PMTCT services located in the catchment of Academic Model Providing Access to Health Care (AMPATH) – a large HIV Comprehensive Care Program run under the auspices of Moi University School of Medicine, located in Eldoret. These facilities implement Option B+ regimen of PMTCT. The approximate coverage of mobile phones in western Kenya is around 78 % [19]. The research setting has been carefully selected to represent urban and rural mixes that have high antenatal HIV percentage prevalence (10–15 %), about twice that of the national prevalence of 6 %.

### Study population

The study population will consist of: (i) pregnant women living with HIV aged 18 and over presenting at ANC for a first visit in the current pregnancy at the selected clinics; and (ii) newborns delivered to these women living with HIV. Women who will be pregnant and will be diagnosed with HIV infection will be referred to a male or female research assistant to complete a checklist for eligibility. Determination of HIV infection will be based on two repeated Determine or Colloidal Gold tests for women newly diagnosed during the current pregnancy, or, based on referral from the comprehensive care clinic for those with known HIV infection and on antiretroviral therapy (ART) or pre-ART). Individuals must fulfill all the inclusion criteria, provide consent to participate and complete an interviewer-administered questionnaire before they are randomized to either the control and intervention groups.

#### Inclusion criteria

Women aged 18 years or aboveEvidence of pregnancyEvidence of HIV infectionResident of the PMTCT clinic catchment area and plans to remain residents from recruitment until 24 months after deliveryWilling to be followed-up from recruitment until 24 months after deliveryOwning a mobile phone or having access to a mobile phoneAble to text message in Kiswahili or have someone in close contact that they trust to read and respond to a text messageWilling to receive text messages from the PMTCT clinic staffAble and willing to provide informed consent

### Intervention

Participants in the intervention group will register their phone numbers in the WelTel system (online or via SMS) and then receive a weekly short text message question in Kiswahili “*Mambo?”* (Kiswahili for “How are you?”) asking about their general wellbeing (Fig. 2). The message will be sent on a fixed day of the week and will allow the patient to respond within 24 h either that they are well for example “*ok”* or “*sawa”* or that they have a problem (for example “problem*”* or “*shida”).* A female study coordinator will be in charge of centrally monitoring the WelTel SMS platform, which automatically sends the messages and registers responses from the participants and categorizes them. All participants who respond “problem” or who do not respond will be directly linked to a regular PMTCT nurse at the woman’s clinic to assist with identified problems. Problems that cannot be immediately resolved by the nurse follow routine procedures at the clinic and are normally referred to the PMTCT clinical officer at the respective facility who will then decide if the patient needs to visit the facility or should receive a follow up phone call. The study coordinator will follow up with the respective PMTCT nurses to record action taken, which is entered directly into the WelTel platform logs as notes. Patients who will not respond to the SMS within 24 h will be traced (first by telephone then at households) within the defaulter tracing outreach program in routine PMTCT care. At enrollment, the participants will be informed that the weekly SMS support service does not replace routine clinic services, and that all appointments made by PMTCT staff should be honored and all emergencies should be handled by usual means. A WelTel SMS platform technician will handle all technical problems that may arise.

**Fig. 2 Fig2:**
[figure not shown]
WelTel SMS intervention

### Outcomes

#### Primary outcome

Retention in PMTCT care is defined as the proportion of women living with HIV and their HIV-exposed infants that remain in care until infants are aged 24 months measured from when the pair is enrolled in the program from the woman’s first visit at ANC until 24 months after birth.

#### Secondary outcomes

Adherence to the WelTel SMS intervention measured as the proportion of women living with HIV who do not respond to the SMS within 7 days.Adherence to (i) ARVs measured as the proportion of women living with HIV who do not respond to the SMS within 7 days when suspected to be out of ARVs (i.e. failure to pick up ARVs that can cover her absence); (ii) facility-based delivery measured as the proportion of women who deliver in hospital; (iii) early infant HIV testing defined as the proportion of HIV-exposed infants who are tested for HIV within 8 weeks of birth measured as HIV –exposed infants with known HIV status at age 10weeks and (iii) exclusive breastfeeding defines as feeding the HIV-exposed infant only milk from the mother’s breast.Participant perceived facilitators and barriers of the WelTel SMS intervention (assessed as perceived reasons and challenges of use as well as suggestions to possible solutions).Cost compared with (i) effectiveness (levels of retention) from a payers’ perspective and (ii) quality of life (differences in pregnant women’s QALYs between the two trial arms.

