### Recruitment

A PMTCT nurse at the selected clinics will inform all consecutive pregnant women identified as living with HIV at their first ANC visit about the study. The PMTCT nurse will then refer these clients to the research assistant who will assess their eligibility and provide detailed information about the study. Individuals who are eligible will be invited to participate in the study and the research assistant will seek their consent.

Participants in the intervention arm who own or have access to mobile phones will be registered directly onto the WelTel platform with their phone number.

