### Data collection and management

All outgoing and incoming text messages will be automatically recorded on the WelTel platform. The platform also captures all of the “problems” noted by participants, instances of non-response, and actions taken in relation to participants’ ‘problem’ responses and non-responses. Platform data will be backed up every 7 days.

All questionnaires will be paper-based and the data manager will then enter data into a database at the central office on an ongoing basis. A data manager will check the forms for completeness and quality will be verified by re-checking a random sample of 10 % of the data. Any problems that arise will be resolved promptly. Participant files will be stored in a locked office at the trial sites.

Data on attendance, HIV care clinical indicators like viral load and CD4 cell count as well as treatment regimen will be collected medical records. We will also collect information on demographic characteristics (age, education level, marital status and parity) of all screened patients/potential trial participants.

Qualitative research using in –depth interviews will also be performed to discover ‘how’ and ‘why’ the intervention works to improve retention in PMTCT program. Purposive sampling will be used to identify participants for qualitative interviews. Face-to-face interactions will be used to build trust during the interview process and to enhance free interaction between the researcher and the participants [20]. All conversations will be recorded with permission from the respondents and the interviews will be performed at a place and in a language preferred by the respondent.

All qualitative research tools will be developed in English, then translated to Kiswahili, and then back translated to English. The interview guide will be available in both languages.

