For the primary outcome, we will compare the proportion of mothers living with HIV and their HIV-exposed infants in the program at 24 months post-birth in the intervention vs. control arm using both parametric (Chi-Square) and exact (Fisher) statistical tests. Secondary outcomes will also be compared between arms, with t-tests for normally distributed variables, Mann Whitney-U tests for non-normally distributed variables, and Chi-Square and Fisher exact tests for categorical variables. The relative risk (RR) for PMTCT retention with 95 % confidence intervals will be computed and the number needed to treat to prevent one non-retained mother-infant pair will also be estimated. Concerning the secondary outcomes, average treatment effects (ATE) will be computed for continuous outcomes and RRs for categorical outcomes. For both primary and secondary outcomes, log-linear or linear regression models will be used to provide effect estimates adjusted for potential imbalances in baseline participants’ characteristics, if required. We will repeat the analysis of primary and secondary outcomes within such subgroups (in relation to socio-demographics) to assess the homogeneity of the intervention effect across pre-determined subgroups of patients. Stratified RRs and ATEs will be computed. Regression models, which include the intervention allocation and subgroup-defining variables and their interaction, will be applied to assess effect modification across groups; all statistics tests will be run based on two side *p*-values and values <0.05 will be considered statistically significant. All statistical analyses will be again performed with Stata version 14.1 (Stata Corporation, College Station, TX, USA).

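### Adherence to ARVs is defined by non-response to an SMS sent only to the intervention arm, so the planned between-arm comparison of this secondary outcome cannot be made as worded

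*Protocol article*

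**What the plan says.** **Definition.** In the protocol article, Secondary outcomes, ARV adherence is component (i) of the second listed outcome. It is measured as the proportion of women "who do not respond to the SMS within 7 days when suspected to be out of ARVs". A parenthesis then describes the suspicion as "failure to pick up ARVs that can cover her absence".

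**Who gets the SMS.** The abstract's Methods paragraph states: "Intervention arm participants will receive an interactive weekly SMS". The Intervention section says: "Participants in the intervention group will register their phone numbers in the WelTel system". The Recruitment section agrees: "Participants in the intervention arm who own or have access to mobile phones will be registered directly onto the WelTel platform". The control arm has standard care.

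**Planned analysis.** Statistical methods states: "Secondary outcomes will also be compared between arms". Relative risks are planned for categorical secondary outcomes, and no secondary outcome is exempted.

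**Other data.** Data collection and management says that "HIV care clinical indicators like viral load and CD4 cell count as well as treatment regimen will be collected" from medical records, along with attendance, with no restriction to one arm. None of these is named as the ARV adherence measure.

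**The concern.** The outcome is tied to an event, replying or not replying to a message, that exists in one arm only. A between-arm relative risk needs the same quantity observed in both arms. If analysts fill the gap by convention, the result will reflect that convention and not the women's ARV supply.

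The definition also has a validity problem inside the SMS arm. It requires non-response in addition to a suspected lapse in supply, so a reply removes a woman from the count whether or not she has collected her drugs.

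At stake is one listed secondary outcome. Because the trial is open, choosing a replacement definition after data have been seen would leave that choice open to challenge.

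**Working it through.** The protocol attaches no numerical figure to this outcome, so there is none to reproduce. The check sets the sections side by side and then follows the definition through the planned relative risk.

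**Inputs**
- Planned women per arm: 300 (Sample size).
- Measure: no reply within 7 days, given suspected lapse in ARV supply (Secondary outcomes).
- SMS recipients: intervention arm only (abstract, Intervention, Recruitment).
- Effect measure: relative risk between arms (Statistical methods).

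**Step 1: what can be observed**

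| | Intervention | Control |
|---|---|---|
| SMS sent | yes | no |
| Reply or non-reply observable | yes | no |
| Pick-up failure observable from clinic records, if abstracted | yes | yes |
| Outcome as worded observable | yes | no |

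As worded, 0 of 300 control women can have an observed value.

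**Step 2: what a convention would produce**

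Suppose there is no true effect. Let f be the proportion with a pick-up failure, equal in both arms, and let r be the probability of no reply within 7 days among such women in the SMS arm. The text does not say whether the denominator is all women or only those with a suspected lapse, so both are shown.

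- Intervention proportion: f × r (all women), or r (women with a suspected lapse).
- Control, with no message scored as no reply: f (all women), or 1 (women with a suspected lapse). The relative risk is (f × r)/f = r, or r/1 = r. Whenever r is below 1 this appears to favour the intervention, although ARV supply is the same.
- Control, with no message scored as no failure: 0 under either denominator. The relative risk has a zero denominator, and any event in the SMS arm counts against the intervention.

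The two conventions point in opposite directions, and neither carries information on ARV supply.

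**Step 3: inside the SMS arm**

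| Pick-up | Reply within 7 days | Counted as non-adherent |
|---|---|---|
| made | yes | no |
| made | no | no |
| missed | yes | no |
| missed | no | yes |

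The third row is the difficulty: a missed pick-up followed by a reply is not counted. The measured proportion among all women is f × r, which cannot exceed the pick-up failure proportion f and falls short of it whenever f is above 0 and r is below 1.

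**Step 4: direction and the companion outcome**

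The first secondary outcome has the same inverted label: "Adherence to the WelTel SMS intervention measured as the proportion of women living with HIV who do not respond". A high value means poor adherence. This outcome also exists only in the intervention arm. That is natural for a process measure, but the general comparison sentence in Statistical methods does not exempt it.

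**The case against.** The strongest reply is the parenthesis on failure to pick up ARVs. It names a criterion that clinics could record in both arms, and one can argue that it states what non-adherence means. If so, control women could contribute. What stands is that a usable criterion is already in the text. What does not stand is that it is the measure: grammatically it explains when a woman is suspected to be without ARVs, and non-response remains the thing counted. If pick-up alone was intended, the text has to say so.

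A second reply is that a full protocol or SAP may settle this. Nothing is being called missing here. The article states a specific definition that conflicts with its own design, and a later document could cure that only by replacing the definition.

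Readers may also infer more than the text supports:
- **That this is a leading secondary outcome.** The article does not rank its secondary outcomes.
- **That a stated objective of showing improved ARV adherence fails.** The Secondary objectives speak only of determining adherence to PMTCT components. The conflict is with the comparison sentence in Statistical methods.
- **That almost every woman would fail the WelTel adherence measure because so many weekly messages are sent.** This needs a rule that a single missed reply counts as failure, assumed reply rates, and independence between weeks. The article gives none of these, and a proportion per message is equally compatible with its wording.

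**Conclusion.** The point holds for ARV adherence as worded. The outcome is undefined for the control arm, 300 of the 600 planned women, or fixed by whatever convention is applied to women who were sent no message. The planned relative risk therefore has no meaning for this outcome. Within the intervention arm, the measure misses lapses in supply that are followed by a reply.

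This rests on two readings of the text: that SMS non-response is the measure and pick-up failure its condition, and that the general sentence on comparing secondary outcomes covers this one. Step 2 of the working assumes equal pick-up failure in both arms, solely to show that an apparent effect can arise without a real one.

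The reach is limited. The primary outcome does not depend on this definition. Facility delivery, early infant testing and exclusive breastfeeding can be measured in both arms. Nor does it follow that the trial can say nothing about ARV adherence: the design allows a common measure from clinic records, but the article does not adopt one.

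**What to change.** 1. Remove the SMS condition from the ARV adherence outcome. Define it identically in both arms from clinic records, using the pick-up criterion already in the text: either failure to pick up ARVs, or the proportion of days covered by pick-ups, over a stated period. Compare arms by intention to treat.
2. Use recorded viral load as supporting evidence only.
3. Report SMS response as a descriptive process measure for the intervention arm, scored as response and not as its inverse. Exempt it explicitly from the between-arm comparison in Statistical methods.

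**Costs.** Wording changes, plus one addition to the planned record abstraction: pick-up dates are not among the items listed in Data collection and management. The result will depend on how complete the records are.

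Two limits should be stated with the new definition. Expected control retention of about 30% means roughly 0.30 × 300 = 90 control women still in care at 24 months and 210 not, so days covered over the whole period would partly repeat the primary outcome. Viral load would be available mainly for women still in care, a group selected after randomisation. Fix the definition and its period before outcome data are examined by arm.
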